## Abstract

**Introduction:**

Motor impairments are the objectively most striking sequelae after stroke, but non-motor consequences represent a high burden for stroke survivors as well. Depression is reported in one third of patients, the fatigue prevalence ranges from 23 to 75% due to heterogenous definitions and assessments. Cognitive impairment is found in one third of stroke patients 3–12 months after stroke and the risk for dementia is doubled by the event.

Aerobic exercise has been shown to reduce depressive symptoms, counteract fatigue, and improve cognitive functions in non-stroke patients. Furthermore, exercise is known to strengthen the immune system. It is unknown, though, if aerobic exercise can counteract poststroke depression, fatigue, poststroke dementia and poststroke immunosuppression. Therefore, we aim to analyse the effect of aerobic exercise on functional recovery, cognition, emotional well-being, and the immune system. Reorganization of topological networks of the brain shall be visualized by diffusion MRI fibre tracking.

**Methods:**

Adults with mild to moderate stroke impairment (initial NIHSS or NIHSS determined at the moment of maximal deterioration 1–18) are recruited within two weeks of stroke onset. Study participants must be able to walk independently without risk of falling. All patients are equipped with wearable devices (smartwatches) measuring the heart rate and daily step count. The optimal heart rate zone is determined by lactate ergometry at baseline. Patients are randomized to the control or the intervention group, the latter performing a heart rate-controlled walking training on own initiative 5 times a week for 45 min. All patients receive medical care and stroke rehabilitation to the usual standard of care. The following assessments are conducted at baseline and after 90 days: Fugl Meyer-assessment for the upper and lower extremity, 6 min-walk test, neuropsychological assessment (cognition: MoCA, SDMT; fatigue and depression: FSMC, HADS-D, participation: WHODAS 2.0 12-items), blood testing (i.e. immune profiling to obtain insights into phenotype and functional features of distinct immune-cell subsets) and cranial magnetic resonance imaging (MRI) with grid-sampled diffusion weighted imaging, white matter fibre tracking and MR spectroscopy.

**Perspective:**

This study investigates the effect of smartwatch-controlled aerobic exercise on functional recovery, cognition, emotional well-being, the immune system, and neuronal network reorganization in stroke patients.

*Trial registration*

ClinicalTrials.gov NCT Number: NCT05690165. First posted19 January 2023. Retrospectively registered, https://clinicaltrials.gov/ct2/show/NCT05690165

## Introduction

### Rehabilitation from acute stroke

The number of stroke survivors is increasing due to the progress in acute treatment. Despite that, stroke incidence shows a shift to younger age groups [9, 10]. Given the high functional demand in this age group and the remaining lifetime compared to patients, who suffer from a stroke at an advanced age, even subclinical sequelae may have a high impact on quality of life. Moreover, non-motor consequences like poststroke depression or poststroke fatigue represent a burden on national economy. It is reported that 70% of stroke survivors remain limited in their work ability [4].

For stroke rehabilitation there are two relevant forms of neuroplasticity: One that is induced by the lesion itself and one which is induced by physical training [6]. For the latter, the earlier the start of rehabilitation the better the functional improvement [19]. In Germany patients usually start—in- or outpatient—rehabilitation around two weeks after the event and it lasts up to four weeks. Especially the patients with non-obvious deficits tend to fall of the grid afterwards. The transition in care and community rehabilitation especially in the mildly affected patients is not always optimal. The rehabilitation for those patients is often regarded as completed. Despite, they are at a high risk for a second vascular event [19].

### Cognitive impairment after stroke, poststroke-depression, and poststroke-fatigue

Cognitive impairment occurs in more than one third of patients 3–12 months after stroke and concerns impairment in attention, processing speed, executive function, verbal and visual memory, language, and perception abilities [19]. These cognitive deficits can individually persist over years. The risk for dementia is doubled by a stroke [8]. Poor physical activity has been identified as a risk factor for dementia [11]. On the other side, physical activity – even on a low-to-moderate level – exerts a protective effect on cognitive decline [16]. Pathophysiologically, this is potentially explained by a change in cytokines such as enhanced levels of brain-derived neurotropic factor, an increased cerebral blood volume as well as a reduction of depressive symptoms by regular exercise [3].

Depression and anxiety are associated with a poorer functional outcome [19]. The prevalence is difficult to determine but reaches up to one third of stroke survivors at any time after stroke [1]. In studies of adults without a stroke, exercise shows a positive effect on depressive symptoms [12]. Exercise may affect the regulation of elevated cortisol levels which result from the dysregulated hypothalamic–pituitary–adrenal axis in depression [12]. In stroke studies depression often serves as a secondary outcome which is why the effect of exercise is difficult to determine. So far, there are indicators of a positive effect on depressive symptoms but also inconsistent results [19].

Poststroke fatigue may coexist with poststroke depression. It is not consensually defined and characterised by an exhausted feeling, emotional instabilities, increased need for rest and consequently less social participation and a subjective lack of physical or mental energy. The prevalence varies from 35 to 92% due to a wide variability across studies in terms of definition as well as time and method of assessment [2]. No proven therapy exists for poststroke fatigue. From other diseases like multiple sclerosis it is well known that physical exercise improves fatigue symptoms [13].

### Role of the immune system in stroke rehabilitation

The ischemic event in the brain induces a neuroinflammatory process. The excessive activation of the autonomic system causes an immunodepression correlating with a lymphopenia and dysfunctional immune cells. Local immune responses and a local sustained inflammation in the brain, such as formation of neutrophil extracellular traps at the borders of the infarct zone, contribute to further neurological deterioration in the subacute and chronic phase [9, 10]. Anti-inflammatory and neuroprotective treatments in the acute and subacute phase are being investigated, but none of them has proven to be effective yet. In general, the anti-inflammatory effects of regular moderate exercise by affection of the immune regulation are well-known [18]. Regular endurance training changes the phenotype of neutrophils to one which resembles a more anti-inflammatory phenotype. Similar effects are described for monocytes, which differentiate more into the non-classical, less inflammatory phenotype upon regular exercise. Regarding the adaptive immunity, it is known that exercise improves regulatory T-cell-function and –numbers [18].

Taking into account the correlation and assumed contribution of a chronic low-grade inflammatory state to typical lifestyle-associated and cardiovascular diseases and the potential of physical activity to modulate the inflammatory state [18], physical activity might be a link to complement direct treatment of typical stroke consequences.

### Effects of exercise in stroke patients

According to current knowledge, cardiorespiratory training exerts a positive impact on motor and cardiovascular function. Positive effects on the activities of daily living, walking distance and walking speed are reported and the American Heart Association (AHA) recommends endurance training with a duration of at least 20 min on 3–5 days per week [15]. Especially aerobic treadmill or walking training is recommended [19].

After a stroke, patients often enter a vicious circle: Stroke patients reach a deconditioned state which leads to physical inactivity, reduced socialization, and an increased risk of future vascular events (including stroke) [19]. At the same time, the activity level after stroke represents an independent predictor of life satisfaction – including patients who are considered to suffer from a mild stroke [5]. In contrast, stroke rehabilitation programs and routine physiotherapy sessions fail to induce a cardiorespiratory training effect of sufficient intensity and duration [7]. Research indicates that exercise exerts a positive impact on fatigue, depression, mental well-being as reflected by social participation, and health-related quality of life [19]. Whereas very early initiation of exercise (within 24 h after stroke) in the AVERT trial was associated with a reduced chance of a favourable outcome at 3 months, an initiation in the subacute phase (a mean of 11–78 days after stroke) is recommended [19].

As mentioned above, the rehabilitation continuity is not ensured after the in- or outpatient rehabilitation directly after the event. The self-reported and self-perceived amount of daily activity of stroke patients is inflated [14]. The role of wearable devices or apps to provide direct feedback concerning the amount of daily activity has not been elucidated.

## Methods

### Aims of the trial

A deconditioned state in stroke survivors is correlating with motor impairments and interacting with frequent stroke sequela like depression, fatigue, and cognitive impairment. A positive effect of aerobic exercise is generally known, but its implementation in stroke aftercare is challenging [19].

Therefore, the objectives of our study are to determine the effect of regularly walking exercise on the rehabilitation of stroke, especially on motor function, cognition, fatigue, and depression as well as immunological effects. If patients benefit, we aim to further determine estimates about specific subgroups of patients, who benefit most, and the amount of exercise to recommend those patients. In this pilot study, we are also interested in the feasibility of the study concept, patient’s adherence, and organisational requirements for a successful implementation.

### Study description and design

This is a single-centre pilot study with two groups. Screening for eligibility takes place at admission to the stroke unit and study inclusion in the first 14 days after ischemic stroke. Every participant receives a lactate ergometry with electrocardiogram (ECG) monitoring and is equipped with a wearable device/smartwatch. Participants in the intervention group conduct a heart rate-controlled walking exercise 5 times weekly for 45 min on own initiative for 90 days. Participants in the control group receive no training requirements. All participants document their daily step count as well as performed exercise paper based. The following tests are performed at baseline and at final visit after 90 days: For assessing cognitive functioning the Montreal Cognitive Assessment (MoCA) and the Symbol Digit Modalities Test (SDMT) are administered. Fatigue and depressive symptoms are assessed by the Fatigue Scale for Motor and Cognitive Functions (FSMC) and the Hospital Anxiety and Depression Scale; German Version (HADS-D). To measure the impact of the health condition on a person's ability to participate in daily activities the World Health Organization Disability Assessment Schedule (WHODAS 2.0) is used. Furthermore, blood samples are collected, and MRI scans are conducted. A flowchart of the study is shown below (Fig. 1).

**Fig. 1 Fig1:**
[figure not shown]
Study flowchart

The study is conducted at the University Hospital Muenster, Department for Neurology with Institute of Translational Neurology.

### Arms and interventions

The intervention consists of a regular, heart-rate-controlled walking exercise 5 times per week for 45 min over a period of 90 days after stroke. The heart rate as well as the daily step count is measured by wearable devices/smartwatches. A lactate ergometry is performed for each participant at baseline to determine to optimal heart rate range for exercising. The examination is performed on a bicycle ergometer and the lactate values are assessed by a hand-held meter (Lactate Scout 4). Baseline lactate values are obtained, and patient conduct a step wise load test. Beginning at a load stage of 50 W we perform a step wise increase of 25 W and a duration of 3 min each. At the end of every stage, lactate values and an ECG are recorded with special attention to excitation regression changes or rhythm disturbances. Patients assign a subjective stress level to each stage after being offered a quantitative scale ranging about six items from “low load” to “very strenuous”. The test is ended after the patient reports a subjective exertion. The evaluation is performed by creating a threshold curve and reading the corresponding heart rate at the level of a lactate value of 3 mmol/l. Patients are told to exercise most of the time in a range of 75–95% of this heart rate value. Patients receiving heart-rate-controlling medications (beta-blockers) are told to rather control the load more according to a subjectively light feeling of exertion. This is done for those patients as well whose evaluation failed due to high baseline lactate values. The daily step count and the performed exercise is documented paper based by the participants.

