### Eligibility criteria

All patients admitted to the hospital with an acute stroke are screened for eligibility. Patients with severe strokes and those who cannot walk independently are not eligible for the study. As it is a pilot study and because we are interested in feasibility of the study concept, the inclusion criteria are set very broad. We also included patients who would likely have difficulty operating the smartwatch.

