### Statistical analysis

We aim to perform a simple linear regression analysis using the averaged amount of exercise as predictor and measurements on day 90 of each test variable as outcome. Baseline measurements and other possible nuisance variables will be included as additional covariates. As prior analyses, we will analyse the amount of exercise across both groups.

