### Weaknesses

The study requires a high motivation by the participants. Adherence to physical activity without direct reward represents a major challenge. One risk of our study is to include preferentially patients with a high premorbid activity level. We tried to minimize this risk by broad inclusion criteria and setting an individual heart rate zone target. Nevertheless, we cannot adjust for the level of activity patients had before the stroke. Another problem is the operation of the wearable device/smartwatch. Especially older patients face trouble with it and were not able to document their daily activity. Another common challenge for investigating the effects in stroke patients suffering from mild to moderate symptoms is that it is difficult to show the effect. Our sample size is not sufficient to meet this challenge, but we aim to show feasibility of the design to translate the project into larger cohorts.

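### Exercise and steps are recorded only on paper by unblinded participants, although every participant wears a watch and the protocol calls self-reported activity inflated

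*Protocol article*

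**What the plan says.** All references are to the protocol article.

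- **Recording.** Study description and design states "All participants document their daily step count as well as performed exercise paper based". Arms and interventions repeats it: "The daily step count and the performed exercise is documented paper based by the participants". No export or read-out of watch data is described.
- **Device.** The Methods part of the abstract states "All patients are equipped with wearable devices (smartwatches) measuring the heart rate and daily step count", and Arms and interventions agrees.
- **Use of the exposure.** Statistical analysis states "We aim to perform a simple linear regression analysis using the averaged amount of exercise as predictor and measurements on day 90 of each test". Those day-90 values are the outcomes, and baseline and other covariates are added. The source and unit of the exercise amount are not named. Aims of the trial lists adherence as an interest and hopes to learn how much exercise to recommend.
- **Reliability of self-report.** Effects of exercise in stroke patients states "The self-reported and self-perceived amount of daily activity of stroke patients is inflated".
- **Difficulty with the device.** Eligibility criteria states "We also included patients who would likely have difficulty operating the smartwatch". Weaknesses, after naming operation of the watch as a problem, states "Especially older patients face trouble with it and were not able to document their daily activity".
- **Blinding.** Randomization says that researchers and patients know the allocation from its disclosure onward.

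**The concern.** The article names a bias in self-reported activity and puts a measuring device on every wrist, then describes only a record written by the participant. Participants are unblinded, and only the intervention arm has a target (5 sessions of 45 min a week) to report against, so reporting error need not be equal in the two arms.

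Three uses of the data depend on this record: the slope of each day-90 outcome on exercise, the description of adherence, and any amount of exercise later recommended. The paper record as described holds steps and performed exercise but not heart rate. Time spent in the individual heart-rate range, which characterises the intervention, is therefore not described as captured at all.

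**Working it through.** The plan states no effect size, power or reliability, and its 30 patients come from no calculation, so there is no figure to reproduce. The first step compares the text; the others are illustrations on assumed inputs.

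**1. Which entries are exposed to which error.** The watch measures steps, so a paper step count is presumably copied from its display. Its main risks are transcription error and omission. A performed-exercise entry is the participant's own account, and the inflation statement applies most directly to it. It is also the nearest match to the predictor's wording.

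**2. Adherence.** The prescribed amount is 5 x 45 = 225 min/week. If a participant truly did 180 min (assumed) and over-reported by 30% (assumed), the record shows 180 x 1.3 = 234 min. Adherence of 180/225 = 80% would appear as 234/225 = 104%.

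**3. Slope, over-reporting in the intervention arm only.** Assumptions: equal arms, true means E (intervention) and C (control), common within-arm SD s, reported exercise multiplied by o in the intervention arm, and outcome linear in true exercise with no other arm effect. Then

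fitted/true slope = [½(o+1)s² + ¼(oE-C)(E-C)] / [½(o²+1)s² + ¼(oE-C)²]

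With s = 60 min/week:

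| E vs C | o | Fitted/true slope |
|---|---|---|
| 225 vs 100 | 1.3 | 10155.6/14106.1 = 0.72 |
| 225 vs 100 | 1.5 | 11921.9/19951.6 = 0.60 |
| 180 vs 90 | 1.3 | 7380/10026 = 0.74 |
| 180 vs 90 | 1.5 | 8550/13950 = 0.61 |

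Setting s = 0 reduces this to a contrast of arm means, (E-C)/(oE-C), which gives 0.65, 0.53, 0.63 and 0.50. That overstates the distortion, because the planned regression is at patient level.

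**4. The direction is not fixed.** If instead only controls over-report by 30% (E = 225, C = 100), the reported difference in means is 225 - 130 = 95. At s = 60 the factor is [½(2.3)(3600) + ¼(95)(125)] / [½(2.69)(3600) + ¼(95²)] = 7108.75/7098.25 = 1.00. At s = 0 it is 125/95 = 1.32.

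**5. Equal over-reporting in both arms.** The slope is multiplied by 1/o: 0.91, 0.80 and 0.67 for 10%, 25% and 50%. This only rescales the predictor, so the correlation and the test are unchanged. It still matters for adherence and for any recommended amount.

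**6. Random recording error and missing records.** Power = Φ(atanh(r√ρ) x √(n-4) - 1.96), with one covariate, two-sided 5% level, true partial correlation r and reliability ρ. For assumed r = 0.5 and n = 30, power is 0.80, 0.69, 0.55 and 0.39 at ρ = 1, 0.8, 0.6 and 0.4. If 6 of 30 had no usable record (assumed) and were left out, n = 24 and power is 0.69 at ρ = 1 and 0.45 at ρ = 0.6. Standard errors grow by 1/√(1-m): 5%, 12% and 20% for m = 10%, 20% and 30% missing.

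**The case against.** A condensed article commonly leaves the definition of a predictor, the retrieval of device data and the handling of missing values to a fuller document. This is also a 30-patient pilot that deliberately included people likely to struggle and openly reports the difficulty. That answers any complaint about missing detail. It does not answer this point, because the paper route is stated positively, twice. Adherence is among the pilot's own interests, and the Weaknesses section does not mention reporting bias.

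Four stronger readings are tempting and are not supported:

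- **That the regression predictor is known to be the paper record.** Statistical analysis names no source. Paper is inferred because it is the only route described.
- **That the slope is biased downward by a known amount.** The over-reporting rates, weekly minutes and within-arm SD above appear nowhere in the documents, and step 4 shows that the direction can change.
- **That older patients failed at the paper record, so the watch would recover them.** Both Weaknesses and Eligibility criteria tie the difficulty to operating the watch. Read-out may lose the same people.
- **That patients without records will be dropped.** No rule for missing exposure is shown, so exclusion from the regression is only an inference.

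The documents also say that the watch measures, not that it stores or exports data.

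**Conclusion.** The point holds in a limited form. The only described source for steps and performed exercise is a paper record kept by unblinded participants, although a device is on every wrist and the article itself distrusts self-report. The exercise entries are open to error that may differ by arm; the step entries mainly to copying error and omission.

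The documents do not determine the direction or size. The factors of 0.60-0.74 apply only if the intervention arm alone over-reports by 30-50%, with the assumed means and an SD of 60 min/week. The power figures rest on assumed correlation, reliability and missingness. The change is worthwhile because it is cheap and protects the adherence result, not because a particular bias has been shown.

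**What to change.** 1. **Source.** Where the watch or its app stores data, have study staff read it out at the 90-day visit in the same way in both arms, and make it the primary source for amount of exercise.
2. **Measure.** Use mean daily steps as the measure available for all patients. Use minutes in the individual heart-rate zone only for those with a valid zone who are told to steer by heart rate. Under Arms and interventions this leaves out patients on beta-blockers and those whose lactate evaluation failed.
3. **Paper record.** Keep it as a back-up, flag every value taken from it, and report its agreement with the watch by arm.
4. **Analysis by arm.** Add a baseline-adjusted comparison of day-90 outcomes by randomised arm. Statistical analysis does not plan one; only the immune profile is framed as a group comparison, under Outcome measures. It needs no exposure record, so patients without one stay in the analysis.

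The cost is a few minutes of staff time per patient. Gaps will remain from device memory, non-wear or difficulty operating the watch, possibly in the same older patients, and should be reported as a feasibility result. Recruitment began in October 2022, so patients already past day 90 can be read out only if their data were kept.
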